## Abstract

**Background:**

Albumin is a multifunctional plasma protein that is mainly synthesized in the liver and may play a neuroprotective role in treating acute ischemic stroke (AIS). The efficacy of albumin in patients with AIS receiving reperfusion therapy remains unknown.

**Methods:**

ARISE is a multicenter, randomized, double-blind, placebo-controlled, phase 2 study. We will recruit 134 patients aged 18–80 years with AIS due to large-vessel occlusion in the anterior circulation, within 24 h of symptom onset, with an Alberta Stroke Program Early CT Score of 3–10 points and an infarct core volume of ≤100 mL at baseline. Eligible patients will be randomly assigned, on a 1:1 ratio, to undergo endovascular therapy (EVT) and receive albumin therapy (0.5 g/kg; intravenous injection) once daily for 4 days or to undergo EVT and receive placebo therapy once daily for 4 days. The primary efficacy outcome is the change in infarct volume from baseline to day 5.

**Conclusion:**

The ARISE trial will provide valuable evidence on the efficacy and safety of albumin in patients with AIS receiving EVT.

**Clinical trial registration:**

www.clinicaltrials.gov, NCT06538844.

## Background

Stroke is the most common cause of death and disability worldwide, with acute ischemic stroke (AIS) accounting for 80% of all cases (1, 2). Effective reperfusion therapies, such as intravenous thrombolysis and endovascular therapy (EVT), have been widely used in the treatment of AIS patients (3–5). While recanalization of occluded arteries is central to the treatment of AIS, patient prognosis may be further improved with additional treatment options that preserve and enhance brain function through neuroprotection (6, 7). Neuroprotective drugs can freeze the ischemic penumbra and target the ischemic cascade following cerebral infarction, including mechanisms such as oxidative stress and inflammation. This may reduce the inflammatory response, limit hemorrhagic transformation, and improve neurological prognosis after cerebral infarction (8, 9). However, neuroprotection in AIS has a long history of clinical trial failures over the past several decades (9, 10). One possible reason is that many of these drugs were not combined with reperfusion therapy (11, 12). Therefore, it is recommended that previously unsuccessful neuroprotective drugs, especially those supported by strong preclinical research evidence and confirmed to be safe in clinical studies, be reconsidered in the context of reperfusion therapy (9).

Albumin, the predominant protein in plasma, is mainly synthesized in the liver (13). Although the exact molecular mechanisms underlying albumin’s effects remain unclear, preclinical studies have shown its neuroprotective effects in several animal models of cerebral infarction. These effects include reducing cerebral edema through dehydration and increasing cerebral blood flow in ischemic areas (14–16). However, the Albumin in Acute Ischemic Stroke (ALIAS) trial, conducted from 2009 to 2012, did not confirm that high-dose albumin improves neurological prognosis in AIS patients (17). In this study, only 21% of participants received EVT. EVT devices and therapeutic techniques, along with the expansion of indications for EVT and the reduction of barriers to EVT selection through imaging, were not fully developed at the time of the study (17). The fact that neuroprotective treatment with albumin was not combined with efficient reperfusion therapy may have contributed to the failure of the study. Therefore, it is important to reevaluate the neuroprotective role of albumin in the context of reperfusion therapy for AIS.

This protocol describes the rationale and design of the ARISE (Albumin for Patients with Acute Large-Vessel Occlusive Stroke Undergoing Endovascular Therapy) trial, which aims to investigate albumin’s safety and efficacy for AIS patients undergoing EVT.

## Methods

### Ethical approval and informed consent

The clinical trial complies with the ethical guidelines outlined in the Declaration of Helsinki, which governs medical research involving human subjects. The ethics committees and institutional review boards of all participating clinical sites approved the study protocol. Prior to participation, written informed consent will be obtained from all participants or their legal guardians.

### Study design

ARISE is a multicenter, randomized, double-blind, placebo-controlled trial with two parallel (1:1) groups (albumin or placebo), designed to evaluate the safety and efficacy of albumin for patients with AIS receiving EVT. All participants will be followed for 3 months. The study has been registered in www.clinicaltrials.gov (registration number NCT06538844).

### Patient population

Patients will be eligible for enrollment if they have an acute ischemic stroke due to a large-vessel occlusion in the intracranial segment of the internal carotid artery or the M1 or M2 segment of the middle cerebral artery. Eligible patients must be aged 18–80 years, have a modified Rankin Scale (mRS) score of ≤1 the onset of the disease, have a National Institute of Health Stroke Scale (NIHSS) score of ≥6, have an Alberta Stroke Program Early CT Score (ASPECTS) of ≥3, and have ischemic core volume of ≤100 mL. Patients must be enrolled up to 24 h after the onset of stroke symptoms. A complete list of inclusion and exclusion criteria is provided in Table 1.

**Table 1 tab1:** Inclusion and exclusion criteria.

Inclusion and exclusion criteria	
Inclusion criteria	Age between 18 and 80 years; Anterior circulation acute ischemic stroke, with acute occlusion of the responsible vessel located in the intracranial segment of the internal carotid artery, or the M1 or M2 segment of the middle cerebral artery; National Institute of Health Stroke Scale (NIHSS) score ≥6; Modified Rankin Scale (mRS) score ≤1 before onset of the disease; Alberta Stroke Program Early CT Score (ASPECTS) ≥ 3 points; Ischemic-core volume ≤100 mL; Patient is treatable within 24 h of symptom onset. Symptom onset is defined as the point in time the patient was last seen well (at baseline) if patients are unable to provide a reliable history, or the point in time when symptoms have started if patients can provide a reliable history. Treatment start is defined as groin puncture; Written informed consent provided by the patients or their legal relatives.
Exclusion criteria	Evidence of intracranial hemorrhage (intracerebral hematoma (ICH), subarachnoid hemorrhage (SAH), epidural hemorrhage, acute or chronic subdural hematoma (SDH)) on the baseline CT or MRI scan; History of congenital or acquired bleeding disorders, coagulation factor deficiency diseases, thrombocytopenic diseases, etc.: Anticipated difficulty in completing endovascular treatment due to vascular tortuosity; Known severe allergy (more severe than skin rash) to contrast agents uncontrolled by medications; Pregnancy and breastfeeding; An episode or exacerbation of congestive heart failure from any cause in the past 6 months; History of heart valve disease complicated by congestive heart failure within the past 6 months; Cardiac surgery with thoracotomy (e.g., coronary artery bypass grafting or valve replacement surgery) within the past 6 months; Acute myocardial infarction in the past 6 months; Signs or symptoms of acute myocardial infarction upon admission, including electrocardiographic findings; Elevated serum troponin concentration upon admission (>0.1 μg/L); Acute arrhythmia (including any tachycardia or bradycardia) with hemodynamic instability (systolic blood pressure <100 mm Hg) upon admission; Acute or chronic lung diseases requiring long-term or intermittent oxygen therapy; Findings on physical examination of any of the following abnormalities: (1) jugular venous distension (jugular venous pulsation >4 cm above the sternal angle); (2) resting tachycardia due to congestive heart failure (heart rate > 100 per/min); (3) third heart sound; (4) abnormal hepatic jugular venous reflux; (5) pitting edema of the lower extremities attributable to congestive heart failure or without apparent cause; (6) rales in both lungs; and (7) or evidence of pulmonary edema, pleural effusion, or pulmonary vascular redistribution on chest X-ray; Known recent or current serum creatinine exceeding 1.5 times the upper limit of normal, or an estimated glomerular filtration rate (eGFR) < 60 mL/min; Refractory hypertension that is difficult to control with medication (defined as systolic blood pressure > 220 mmHg, or diastolic blood pressure > 110 mmHg); Severe chronic anemia (hemoglobin < 75 g/L); History of albumin allergy or known allergy to albumin; Patients with severe mental disorders or dementia who are unable to cooperate in completing informed consent and follow-up content; The expected survival time is less than 90 days (such as comorbidity with malignant tumor or severe systemic diseases); Patients who participated in other interventional clinical studies within 30 days prior to randomization or are currently participating in other interventional clinical studies.

### Randomization

Eligible patients will be randomly assigned (1:1) to receive albumin or placebo via a web-based interactive response system. A minimization process will be used to balance the stratification factors of age (≤ 60 or > 60 years) and baseline ASPECTS (3 to 6 or ≥6) at each medical site.

### Treatments

After qualifying imaging, patients will undergo EVT using currently available devices as quickly as possible and will receive intravenous thrombolysis if indicated (before or during EVT, at a primary hospital prior to transfer, or at the comprehensive stroke center). The experimental group will receive a 25% albumin solution (0.5 g/kg; maximum dose 150 mL) administered via intravenous infusion once daily for 4 days. The control group will receive an equivalent volume of placebo injection intravenously once daily for the first 4 days (Figure 1). The trial drugs will be manufactured and provided by Shanghai RAAS Blood Products Co., Ltd., Shanghai, China. All researchers and patients will be blinded to treatment allocation. The slightly differently colored study drugs will be concealed. The first infusion will be administered within 1 h after randomization. The steering committee will make recommendations for concurrent treatments. Equal care following the American Heart Association/American Stroke Association guidelines for AIS during admission will be provided for all patients.

**Figure 1 fig1:**
[figure not shown]
Graphical study design. NIHSS, National Institute of Health Stroke Scale; mRS, Modified Rankin Scale; ASPECTS, Alberta Stroke Program Early CT Score.

### Study outcomes

The primary efficacy endpoint is the change in infarct volume from baseline (as measured by computed tomography perfusion (CTP)) to day 5 (as measured by fluid-attenuated inversion recovery (FLAIR)). Infarct volume assessed by CTP will be calculated using NeuBrainCARE^®^ software (version 1.0, Neusoft, Beijing, China). All investigators responsible for enrollment will receive training on the imaging protocol and on the use of NeuBrainCARE^®^ software. For the baseline assessment, the infarction core volume will be considered to be those areas with a relative cerebral blood flow (rCBF) of less than 30%, as indicated by CTP. FLAIR images will be used to calculate the infarct volume at follow-up. If magnetic resonance imaging (MRI) at follow-up time is unavailable, computed tomography (CT) can be used.

The secondary efficacy outcomes include (1) early neurological improvement within 24 h: a decrease in NIHSS score of ≥8 points or NIHSS score of 0–2 within 24 h (2); neurological deterioration within 24 h: an increase in NIHSS score by ≥4 points within 24 h (3); NIHSS score at 24 h (4); proportion of successful reperfusion (mTICI 2b/3) (5); NIHSS score at 5 days (6); proportion of patients with functional independence (mRS 0–1) (7); mRS of 0–2 at 90 days (8); European quality of Life-5 dimensions (EQ-5D) at 90 days; and (9) proportion of patients with Barthel Index (BI) of 95–100 at 90 days. The safety endpoints will mainly include (1) intracerebral hemorrhage within 24 h (2), symptomatic intracerebral hemorrhage (ICH) within 24 h (3), new-onset atrial fibrillation within 5 days (4), pulmonary edema or congestive heart failure within 5 days (5), intracerebral hemorrhage within 5 days (6), decompressive craniectomy within 7 days (7), death within 90 days (8), adverse events (AEs), and (9) serious adverse events (SAEs).

### Sample size calculation

In historical controls, the mean growth in the post-EVT infarct core volume from baseline is 18.7 mL, with a variance of 9.7. Based on our pilot study (unpublished data), we assume that there will be a 30% reduction in infarct volume in the albumin group compared to the sham group. A sample size of 128 participants would provide the trial with 90% power at a two-sided alpha level of 0.05. Considering a 5% loss to follow-up, the total sample size estimate was 134 participants (67 per group).

### Statistical analysis

The main analysis will be performed in the intention-to-treat population. The primary efficacy outcome will be analyzed by a linear regression model or median regression model, depending on the distribution, to compare the change in infarct volume from baseline to day 5 between the intervention group and the control group, after adjusting for baseline ASPECTS, age, and baseline infarct core volume. The effect of the intervention is presented as a mean difference (or median difference) and 95% confidence intervals (CIs). For missing infarct volume data due to stroke-related death, the worst infarct growth will be imputed. Other missing data will be handled using multiple imputation.

For other outcomes, continuous variables will be analyzed using the same method as the primary efficacy outcome, and a mean difference (or median difference) with 95% CIs will be calculated. Binary variables will be estimated using a modified Poisson regression model, and the result will be presented as relative risk and corresponding 95% CIs. All analyses will be conducted at a two-sided level with a significance level of 0.05. Statistical tests will be performed using the R programming language (version 4.3.3).

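### As written, NIHSS at 24 h and day 5 are analysed without baseline NIHSS; a smaller point is that allocation is minimized within site but no model names site

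*Protocol article*

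**What the plan says.** - **Primary model** (Protocol article, Statistical analysis): linear or median regression of infarct growth "after adjusting for baseline ASPECTS, age, and baseline infarct core volume".
- **Other continuous outcomes** (same section): "continuous variables will be analyzed using the same method as the primary efficacy outcome". By the Study outcomes section, these include NIHSS at 24 h and at 5 days.
- **Binary outcomes** (same section): "Binary variables will be estimated using a modified Poisson regression model". No covariates are named.
- **Allocation** (Randomization): "A minimization process will be used to balance the stratification factors of age" and of baseline ASPECTS, "at each medical site". NIHSS is not a balancing factor.
- **Availability of baseline NIHSS**: a score of at least 6 is an entry criterion (Table 1), and the score is recorded at baseline, 24 h and day 5 (Table 2).
- **Sample size** (Sample size calculation): "A sample size of 128 participants would provide the trial with 90% power".

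**The concern.** The primary model adjusts for the baseline value of its own outcome, the infarct core volume. Carried over unchanged to NIHSS, the same covariate list keeps the infarct baseline and omits the NIHSS baseline. A patient's own baseline score is usually among the best predictors of the follow-up score, so omitting it widens the interval. It also leaves any chance difference in stroke severity between two arms of 67 uncorrected, except for the part that age, ASPECTS and core volume happen to capture. These outcomes are early clinical evidence in a phase 2 trial meant to inform a phase 3 decision.

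Separately, balancing within site tends to equalize the arms inside each site. If site predicts infarct growth, a model without site puts that between-site variation into the error term, and the reported standard error is then larger than the true one.

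**Working it through.** **1. The plan's own figure.** Effect = 0.30 × 18.7 = 5.61 mL. The stated spread ("the mean growth in the post-EVT infarct core volume from baseline is 18.7 mL, with a variance of 9.7") reproduces the sample size only if 9.7 is read as a standard deviation. With "90% power at a two-sided alpha level of 0.05", the normal formula 2 × (1.960 + 1.282)² × 9.7² / 5.61² = 62.8 gives 63 per arm. The t-based version gives 64 per arm, or 128, as stated. This is an unadjusted comparison of two means, so the stated 128 relies on neither site nor NIHSS.

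**2. Baseline NIHSS.** Let r be the partial correlation of baseline with follow-up NIHSS, given age, ASPECTS and core volume. The documents give no value, so r is an assumption. Adding the covariate multiplies residual variance by 1 − r² and interval width by √(1 − r²). The equivalent sample size is 128 / (1 − r²).

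| r (assumed) | 1 − r² | CI width × | Equivalent n | Gain |
|---|---|---|---|---|
| 0.3 | 0.91 | 0.95 | 141 | 10% |
| 0.4 | 0.84 | 0.92 | 152 | 19% |
| 0.5 | 0.75 | 0.87 | 171 | 33% |
| 0.6 | 0.64 | 0.80 | 200 | 56% |

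**3. Chance imbalance in NIHSS.** With 67 per arm, the standard error of a standardized baseline difference is √(2/67) = 0.17 SD. A gap above 0.2 SD has probability 2 × [1 − Φ(0.2/0.173)] ≈ 0.25, about one trial in four, if NIHSS is unrelated to the minimization factors. If that gap lies in the part of NIHSS not explained by the other covariates, it shifts the estimate by 0.2 × r, that is 0.06 to 0.12 residual SD for r of 0.3 to 0.6. The 95% half-width is about 1.96 × 0.173 = 0.34 SD.

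**4. Site, analytic.** Assume perfect balance within site and intraclass correlation ρ (not given in the documents). The model without site overstates the standard error by 1/√(1 − ρ). Its true type I error is 2 × [1 − Φ(1.96/√(1 − ρ))].

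| ρ (assumed) | SE too large by | Type I error | Power without site | Power with ideal site adjustment |
|---|---|---|---|---|
| 0.02 | 1.0% | 0.048 | 90.7% | 91.1% |
| 0.05 | 2.6% | 0.044 | 91.1% | 91.9% |
| 0.10 | 5.4% | 0.039 | 91.7% | 93.2% |
| 0.20 | 11.8% | 0.028 | 92.9% | 95.5% |

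Across this range the loss is about 0 to 3 power points.

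**5. Site, simulated.** The number of sites is not given either. The settings were 128 patients, minimization within site with a 0.8 biased coin, SD 9.7, 8, 15 or 30 sites, ρ from 0 to 0.20, and 3,000 runs each. Models included age and ASPECTS, with or without fixed site effects. Without site, type I error was 0.036 to 0.044 at ρ = 0.05 and 0.038 to 0.040 at ρ = 0.10, which agrees with step 4. Mean 95% interval widths in mL, without and then with fixed site effects:

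- 8 sites, ρ = 0.10: 6.73 and 6.48
- 15 sites, ρ = 0.02: 6.80 and 6.84
- 30 sites, ρ = 0.05: 6.82 and 6.97
- 30 sites, ρ = 0.20: 6.79 and 6.40

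Fixed effects widened the interval in 6 of the 15 settings, all with ρ of 0.05 or less. A random intercept was not simulated.

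**The case against.** **The shared method may mean only the type of regression.** The primary model adjusts for its own outcome's baseline, so a sympathetic reader could assume the NIHSS models do likewise. That reading is possible, but it is not stated. The only covariate list in the article omits NIHSS, so the point needs at least one clarifying sentence.

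**The size rests on assumed values.** This stands. At r = 0.3 the gain is only 5% in interval width, and the documents support no particular r. These are also two of nine secondary efficacy outcomes in a trial powered on infarct growth.

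**Site is the level of balancing, not one of the two named factors, and both named factors are in the primary model.** This is true and limits the site point. A reader might infer that leaving out site wastes much of the benefit of the allocation. Steps 4 and 5 do not support that: the loss is small, and with many small sites and a low intraclass correlation fixed effects can cost precision. A random intercept also does not transfer directly to median or modified Poisson regression.

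**Silence on covariates for the binary outcomes is not an error.** This stands. A condensed article may leave that list to the analysis plan. A reader might infer that every modified Poisson model should carry the same covariates, but sparse safety events at 67 per arm may not support them. Early improvement and deterioration also already use the baseline score, at least in part, through their change criteria.

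**Conclusion.** The point holds for efficiency. As written, the two continuous NIHSS outcomes lack their own baseline. Adding it would narrow their intervals by about 5 to 20%, if the partial correlation is 0.3 to 0.6. The site omission is real but modest: a standard error about 3 to 5% too large at an assumed intraclass correlation of 0.05 to 0.10, giving a slightly conservative primary test.

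Two stronger conclusions are tempting but unsupported. One is that the primary test or the sample size is compromised: type I error is not inflated, and 128 comes from an unadjusted calculation. The other is that the NIHSS analysis is as inefficient as it could be: it keeps age, ASPECTS and core volume, and a wholly unadjusted model would generally do worse.

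**What to change.** 1. State that the models for NIHSS at 24 h and day 5 include baseline NIHSS, and keep age and ASPECTS.
2. Where linear regression is used, include site as a random intercept, or as a fixed effect with small sites pooled by a rule set in advance. If median regression is chosen, specify separately how site is handled.
3. Do not impose one covariate set on all modified Poisson models, least of all on rare safety events. Leave that list to the analysis plan.

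Baseline NIHSS is already scheduled and site is known from the allocation, so no new data are needed. The NIHSS change costs a sentence. The site change also needs a pooling rule and a short specification for median regression. All of it should be fixed before unblinding, and the sample size need not change.

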## Discussion

Our trial aimed to evaluate the safety and efficacy of albumin intravenous infusion for AIS patients who are receiving EVT. The study was designed with lessons learned from previous studies that failed to prove the effectiveness of the treatment (17). First, our trial ensures that all enrolled patients will undergo EVT and assess recanalization rates. Second, in the ALIAS trial, patients treated with albumin experienced a higher incidence of pulmonary edema and congestive heart failure compared to those treated with saline. According to the results of our pilot study, administering an albumin dose of 2 g/kg (as in the ALIAS trial) as four separate injections of 0.5 g/kg, given continuously over 4 days, results in a greater reduction in infarct volume and fewer adverse reactions. We anticipate that this modified dosing strategy will reduce the likelihood of pulmonary edema and congestive heart failure.

The ARISE trial will enroll patients with an infarct core volume of less than 100 mL, encompassing both small and large core infarcts. The inclusion of patients with a small infarct core volume is consistent with numerous studies, such as the ACTION II trial (Natalizumab in acute ischemic stroke) and the ApTOLL study, in patients with AIS (18, 19). Patients with large core infarcts are more prone to developing cerebral edema, which can lead to further ischemic damage (20). Albumin increases plasma colloid osmolality and has been widely supported in animal studies to reduce cerebral edema and improve neurological prognosis (14). Including patients with large core infarct volumes will provide an answer to the question of whether albumin is effective for patients with large core infarct volumes (20). The benefits of expanding the time window for patients to use neuroprotective medications are worth waiting for. Therefore, the ARISE study sets the treatment window at 24 h. Subsequent subgroup analyses may focus on age, infarct volume, last known good status to randomization time, NIHSS score, and stroke type.

The primary endpoint of the study is the change in infarct volume from baseline to day 5 in the intervention versus control groups. An increase in infarct volume (instead of clinical assessment at 3 months) was chosen because this biomarker is recommended by the Academic Industry Roundtable on Stroke Care and the Stroke Imaging Study (21, 22). It is an objective outcome and may be closely associated with clinical outcomes.

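### Modified Poisson relative risks are set for every binary outcome, but if one arm has no events the model returns a meaningless interval and a near-zero P value

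*Protocol article*

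**What the plan says.** The second paragraph of Statistical analysis in the protocol article deals with everything other than the primary outcome. It opens "For other outcomes, continuous variables will be analyzed using the same method as the primary efficacy outcome" and continues "Binary variables will be estimated using a modified Poisson regression model, and the result will be presented as relative risk and corresponding 95% CIs". It names no exception for sparse outcomes. The same paragraph adds "All analyses will be conducted at a two-sided level with a significance level of 0.05" and specifies R 4.3.3.

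Study outcomes lists nine safety endpoints. Four of the binary ones may be rare in this population: symptomatic intracerebral hemorrhage within 24 h, new-onset atrial fibrillation within 5 days, "pulmonary edema or congestive heart failure within 5 days", and decompressive craniectomy within 7 days. Sample size calculation gives 134 patients, 67 per group. No expected rate is stated for any safety endpoint.

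**The concern.** Modified Poisson regression is a Poisson model with a log link, fitted to binary data, with a robust (sandwich) variance. It works well when both arms have a reasonable number of events. When one arm has none, the log relative risk runs off to infinity and the software stops at an arbitrary large value. An ordinary model-based standard error would become huge and so warn the reader. The robust one does not: it stays near the square root of 1 over the number of events in the other arm. Dividing an arbitrary large estimate by a small standard error gives an extreme test statistic, in whichever direction the events fall.

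At stake is the reading of the rare safety outcomes. A split such as 1 v 0 or 2 v 0, which carries almost no information, would come out of the stated analysis as significant at the stated 0.05 level. A split such as 6 v 0, which deserves attention, would come with an unusable relative risk and interval. Pulmonary edema and heart failure are among the outcomes exposed, and the Discussion gives them particular weight: "We anticipate that this modified dosing strategy will reduce the likelihood of pulmonary edema and congestive heart failure".

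**Working it through.** **Inputs.** From the article: 67 per arm, modified Poisson regression, two-sided 0.05, R 4.3.3. Assumed: the usual meaning of modified Poisson (log link, sandwich variance), since the variance estimator is not spelled out, and the event rates, since none is given.

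**The plan's own figure.** The article states no figure for binary outcomes, only the sample size. With a difference of 0.30 × 18.7 = 5.61 mL and 9.7 read as the standard deviation, the t-based formula gives 63.8, so 64 per arm or 128. Then 128 × 1.05 = 134.4, in line with 134, or 67 per arm. Nothing below depends on that calculation beyond the 67.

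**Why the robust standard error stays small.** Take 0/67 against k/67. The arm with events contributes 1/k − 1/67 to the robust variance of the log relative risk. The empty arm contributes 1/67. The sum is 1/k, so the standard error is √(1/k): 1.00 for k = 1, 0.71 for k = 2, 0.58 for k = 3. Reversing the coding of the arms can lose the empty arm's term numerically, giving 0.99, 0.70 and 0.56. The conclusion is the same.

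**Refit in R 4.3.3, unadjusted, HC0 variance.** The program reported convergence every time.

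| Events | log RR | robust SE | robust P | Fisher P | Newcombe risk difference (95% CI) |
|---|---|---|---|---|---|
| 0 v 1 | −18.1 | 1.00 | 3e-73 | 1.000 | 1.5% (−4.1 to 8.0) |
| 0 v 2 | −17.8 | 0.71 | 1e-139 | 0.496 | 3.0% (−2.9 to 10.2) |
| 0 v 3 | −18.2 | 0.58 | 5e-218 | 0.244 | 4.5% (−1.7 to 12.4) |
| 0 v 4 | −18.5 | 0.50 | 4e-299 | 0.119 | 6.0% (−0.6 to 14.4) |
| 0 v 5 | −18.7 | 0.45 | prints as 0 | 0.058 | 7.5% (0.6 to 16.3) |
| 0 v 6 | −18.9 | 0.41 | prints as 0 | 0.028 | 9.0% (1.7 to 18.2) |

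The model-based Poisson P in these fits is between 0.995 and 0.997, so the false significance comes from the robust variance. HC3 does not help (0 v 1: P = 4e-71). Nor does adjustment for three simulated covariates, run in Python's statsmodels (0 v 2: P = 4e-175).

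**The estimate depends on the software.** For 0 v 3, R gives a 95% interval for the relative risk of exp(−18.1965 ± 1.96 × 0.5774), about 4.0e-9 to 3.9e-8. The same model in statsmodels stops at −21.39 and gives 1.7e-10 to 1.6e-9. The two intervals do not overlap, although the data are identical.

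**How often it happens.** With a true rate p in both arms, one arm is empty with probability z = (1 − p)^67, and exactly one arm is empty with probability 2z(1 − z).

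| Assumed rate p | z | exactly one arm empty | type I error of the stated test |
|---|---|---|---|
| 0.5% | 0.715 | 41% | 0.41 |
| 1% | 0.510 | 50% | 0.50 |
| 2% | 0.258 | 38% | 0.38 |
| 3% | 0.130 | 23% | 0.23 |
| 4% | 0.065 | 12% | 0.12 |
| 5% | 0.032 | 6% | 0.07 |
| 6% | 0.016 | 3% | 0.04 |
| 8% | 0.004 | 0.7% | 0.03 |

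The last column enumerates all tables and adds the few rejections that occur with events in both arms. These figures are per outcome. The type I error of Fisher's test stays at or below 0.025 over assumed rates from 0.5% to 10%.

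**With a true difference.** If the rates were 5% and 1%, z is 0.032 and 0.510, and exactly one arm is empty with probability 0.032 × 0.490 + 0.510 × 0.968 = 0.51. The stated model then has no usable relative risk in half of trials.

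**The case against.** The strongest objection is that this belongs in the statistical analysis plan, which is not shown. A journal article normally names the general model and leaves a sparse-data fallback to the fuller document, and modified Poisson is a standard method. This stands in part: the fuller plan may hold such a fallback. But the article states a rule for all binary outcomes without qualification, and for an empty arm that rule gives a wrong answer. That is more than an omitted detail.

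Second, the problem needs low event rates, which the documents do not give. This stands. The cardiac exclusions in Table 1 may lower the rates, but by how much is unknown, and from about 6% the inflation is gone.

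Third, a relative risk of about 10^8 or 10^-8 printed beside counts of 1 and 0 would look like a failed fit to any careful reader. This also stands, so a reader should not infer that a 1 v 0 split would be accepted as overwhelming evidence. The more realistic harm is that the method is replaced after the data are seen, on a safety outcome.

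Two stronger readings are tempting. A reader might infer from the Discussion that the trial tests whether split dosing lowers pulmonary edema and heart failure. It cannot, because the comparison is split-dose albumin against placebo and there is no single-dose arm. The Discussion states an expectation relative to an earlier trial. A reader might also infer that the relative risk is unreliable whenever events are few, because the most extreme tables drop out. That is true of any relative risk restricted to tables with events in both arms and is no fault of this model.

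**Conclusion.** The point holds for outcomes with an empty arm. At 67 per arm the stated model then returns P below 1e-70 for as little as 1 v 0, where Fisher's test gives 1.0. The significance is false up to about 5 v 0 (Fisher 0.058). From 6 v 0 Fisher agrees that there is a difference (0.028), but the relative risk and its interval remain meaningless.

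How likely this is rests on assumed rates. It matters at about 4% or less per arm (12% to 50% of trials per outcome for rates between 0.5% and 4%), is marginal at 5%, and is negligible at 8% or more. It also rests on reading modified Poisson in its usual sense. The primary analysis is unaffected, as are the commoner binary outcomes such as reperfusion, mRS and Barthel categories. The documents do not support a broader criticism of modified Poisson in this trial. The text should be changed, but the trial's main conclusion does not depend on it.

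**What to change.** Add one sentence to Statistical analysis. Modified Poisson stays for binary outcomes with adequate events in both arms, including safety outcomes that prove common enough, such as any intracerebral hemorrhage and death. For any binary outcome with no events in an arm, or below a small count set in advance (for example fewer than 5 in either arm), report the counts and the risk difference with a score-based 95% CI (Newcombe or Miettinen-Nurminen). If a test is wanted, use an exact P value and name it in advance as the deciding one. That last clause is needed because the two can disagree: at 5 v 0 the Newcombe interval is 0.6% to 16.3% while Fisher P is 0.058. The demonstrated failure is at zero events; the threshold of 5 is a matter of judgement and only has to be fixed beforehand.

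If the full analysis plan already contains such a fallback, confirm it and bring the article's wording into line. Either way, settle it before unblinding.

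The cost is one sentence and standard R functions. The small downside is that sparse outcomes are summarised as risk differences rather than relative risks, so the safety table mixes two scales.
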